#### Primary outcomes: quantitative

Recruitment: the CI will obtain data on the proportion of women agreeing to participate in the trial and the site of recruitment from the research database and Excel spreadsheet chart after completion of the pilot study and will report the data on Microsoft Excel spreadsheet charts (see “Study setting and recruitment”).Retention rate: dropouts and the reasons for withdrawal if known will be documented by the CI on case report forms (CRFs) throughout the pilot trial. New participants will not replace dropouts. Data on the proportion of women who complete the study will be collected from CRFs at the end of the study (see “Data management” and “Statistical analysis”).Compliance: the rates of adherence to probiotic/placebo intake, electronic questionnaires/evaluation form/cry diary and microbial, vaginal and hair samples will be recorded by the CI on CRFs and Microsoft Excel spreadsheet charts throughout the study (see also “Strategies to improve adherence to intervention protocol for information”).Participants’ impressions and experiences: participants will be requested by the CI to fill in a self-created evaluation form within 1 week after completion of the pilot trial at home. The questionnaire includes nine questions: five questions on how the woman experienced (1) filling in questionnaires during the pilot trial (i.e. length, number of questionnaires, electronic method), (2) collecting their own and infant stool samples and vaginal samples (i.e. number of samples, explanation about method of collection, potential difficulties in collecting samples) and (3) having hair samples collected. Four items measure level of satisfaction: two open-ended questions stating “Regarding the study in general, which aspects did you experience as most positive and negative?” and “Do you have any general remarks regarding execution and organization of this study?”. For the other two questions, participants rate the perceived burden of the trial on a scale of 0–10 (0 “no burden”, 10 “very large burden”) and likelihood of participating in a similar trial in the future (0 “no chance of future participation”, 10 “very high chance of future participation”).

#### Primary outcome: qualitative

Data collection for qualitative outcomes will consist of face-to-face and telephone interviews conducted by the CI. At the end of the home visit at baseline (t0), the CI (a physician experienced in research and patient consultations) will ask participants face-to-face the timing and reasons for deciding to join the study (“When did you make the decision to join the PIP pilot trial?” “Why did you choose to join the PIP pilot trial?”). Responses will be noted and directly checked by participants for accuracy. To determine the reasons for non-participation , the CI will ask women who refuse to participate by telephone their reason(s) for non-participation. Responses will be directly transcribed by the CI and not audiotape-recorded. Microsoft Excel spreadsheet charts will be created with (refusing and participating) women (in the rows) and recruitment outcomes (in the columns).

#### Secondary outcomes

In addition to the primary objective, this pilot trial includes six secondary objectives to ensure that certain data can be collected and to exploratorily assess whether maternal probiotic intake, compared to placebo, potentially has an effect on (1) depressive and/or anxiety symptoms, (2) maternal stress (i.e. reported and hair cortisol), (3) maternal vaginal and intestinal microbiota, (4) maternal bonding to offspring, (5) infant microbiota and (6) infant crying. In the absence of a core outcome set to measure potential effectiveness of probiotics on maternal mood, we choose outcome measures that have shown good psychometric properties and have been previously used to assess depressive symptoms, anxiety and stress in RCTs including non-pregnant [6, 28] and pregnant women [36]. Similarly, outcome measures used to assess maternal bonding to offspring and infant crying have been shown reliable in previous studies [36–38]. Regarding the rationale for the choice of biological outcomes, please see “Discussion”. Given that the main aim of this pilot trial is to assess feasibility and acceptability, and not probiotic effectiveness, no criteria will be set for comparison of treatment success between the two treatment arms (probiotic versus placebo) for any of the secondary outcomes. Figure 1 shows the secondary outcomes measured throughout the study. Table 2 displays the secondary outcome measurement variables, participant level analysis metric and methods of aggregation at specific measurement time points of interest. Participants will fill in all questionnaires electronically, except for the Baby’s Day Diary, in order to improve data accuracy and the timelines for receiving data. For data collection forms (instructions and CRFs) see Additional file 2A-E.

**Table 2 Tab2:** Secondary outcome measurement variables, participant level analysis metric and methods of aggregation at specific measurement time points of interest

Secondary outcome	Measurement variable	Participant-level analysis metric^a^	Method of aggregation for each probiotic/placebo treatment arm
Demographic information	History of atopy (mother)	Baseline value	Proportion of participants with positive history of atopy at baseline
	History of atopy (father)	Baseline value	Proportion of fathers with positive history of atopy at baseline
	History of psychiatric disorders	Baseline value	Proportion of participants with positive history of depression or anxiety disorder at baseline
	Number of previous pregnancies	Baseline value	Mean (SD) at baseline
	Age	Baseline value	Mean (SD) at baseline
	Number of previous children	Baseline value	Mean (SD) at baseline
	Type of marital status	Baseline value	Proportion of participants in relationship (i.e. married/living together) at baseline
	Employment status	Baseline value	Proportion of participants employed at baseline
	Education level	Baseline value	Proportion of participants with primary school, lower secondary vocational education, lower secondary education, higher secondary education, middle level vocational education or tertiary education at baseline
	Ethnicity	Baseline value	Proportion of participants whose fathers and mothers were born in the Netherlands at baseline
	Current psychiatric diagnosis	Baseline value	Proportion of participants with diagnosis depression, anxiety disorder, none or other at baseline
Breastfeeding	Exclusive or partial breastfeeding	End value	Proportion of participants with exclusive breastfeeding and partial breastfeeding at 4 weeks postpartum (t4)
Maternal medication use and treatment	Number of non- pharmacological treatment(s) (i.e. cognitive behavioral therapy, psychotherapy, rapid eye-movement therapy, psychosocial support)	Baseline value; change from baseline to t1	Proportion of participants receiving non-pharmacological treatment at baseline; proportion of participants starting new non-pharmacological treatment between t0 and t1
	Number of pharmacological treatment(s) for depression or anxiety	Baseline value; change from baseline to t1	Proportion of participants receiving antidepressants, anxiolytics, other; proportion of participants starting new pharmacological treatment(s) for depression or anxiety between t0 and t1
	Type of general medication used	Baseline value; change from baseline to t1	Proportion of participants taking medication (other than pharmacological treatment for depression or anxiety); proportion of participants who start taking new medication between t0 and t1
	Type of food supplement(s) used	Baseline value; change from baseline to t1	Proportion of participants taking food supplements; proportion of participants who start taking new food supplements during the intervention period
	Type of vitamin(s) used	Baseline value; change from baseline to t1	Proportion of participants taking vitamins; proportion of participants who start taking new vitamins during the intervention period
Maternal lifestyle	Smoking (yes/no)	Baseline value	Proportion of participants smoking
	Alcohol (yes/no)	Baseline value	Proportion of participants drinking alcohol
Pregnancy characteristics	Occurrence of infections during pregnancy	Final value	Proportion of participants reporting infections (i.e. influenza, fever, diarrhea) throughout the study
Delivery characteristics	Gestational age	Final value	Gestational age at delivery
Pregnancy and delivery complications	Number of pregnancy and delivery complications (i.e. hypertensive disorders of pregnancy (pregnancy induced hypertension, preeclampsia, eclampsia, hemolysis - elevated liver enzymes - low platelet count (HELLP) syndrome), gestational diabetes mellitus, preterm birth, cesarean section, retention placentae, hemorrhage postpartum, small or large for gestational age (birth weight < p10 or > p90), puerperal fever, prolonged labor, premature rupture of membranes)	Final value	Proportion of participants diagnosed with pregnancy or delivery complications at delivery
Infant antibiotic use	Number of antibiotics used	Final value	Proportion of infants receiving antibiotics during first month of life
Depression	Edinburgh Postnatal Depression Scale (EPDS) score	Change from baseline to t1 and t4	Mean (SD)/median (IQR)
Depression/cognitive reactivity	Leiden Index of Depression Sensitivity-Revised (LEIDS-R) score	Change from baseline to t1 and t4	Mean (SD)/median (IQR)
Pregnancy related anxiety	Pregnancy Related Anxiety Questionnaire-Revised (PRAQ-R) score	Change from baseline to t1	Mean (SD)/median (IQR)
General anxiety	State-trait Anxiety Inventory (STAI-S) score	Change from baseline to t1 and t4	Mean (SD)/median (IQR)
Pregnancy-related daily hassles	Pregnancy-related daily hassles (PES) score	Change from baseline to t1 and t4	Mean (SD)/median (IQR)
General daily hassles/stress	Daily Hassles List (APL) score	Change from baseline to t1 and t4	Mean (SD)/median (IQR)
Mother to infant bonding	Maternal Antenatal Attachment Scale (MAAS) score	Change from baseline to t1	Mean (SD)/median (IQR)
	Maternal Postnatal Attachment Scale (MPAS)	Change from t3 to t4	Mean (SD)/median (IQR)
Biological samples	Maternal fecal samples (microbiota)	Change from baseline to t1	Relative abundance and diversity of bacteria at phylum up to genus level
	Maternal vaginal samples (microbiota)	Change from baseline to t1	Relative abundance and diversity of bacteria at phylum up to genus level
	Maternal hair (cortisol)	Change from baseline to t1	Mean (SD)/median (IQR)
	Fecal sample infant (microbiota)	Change from t3 to t4	Relative abundance of bacteria at phylum up to genus level
Cry diary	Duration (hours/minutes) of crying during 3 days	Final value	Mean (SD)/median (IQR)

^a^Baseline: t0; time point 1: t1, time point 3: t3, time point 4: t4

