**Methods:**

The Probiotics in Pregnancy (PIP) pilot trial is a double-blind, placebo-controlled, randomized pilot trial. While one group orally consumes a probiotic mixture (Ecologic® Barrier; 2,5 × 109 colony forming units/g; 2 g; daily), the other group consumes a placebo, from between 26 and 30 weeks gestation until delivery. Subjects are randomly allocated (1:1) to the intervention or placebo group. Forty healthy pregnant women with symptoms of depression or anxiety and uncomplicated pregnancies at randomization will be included. The primary aim is to determine the feasibility and acceptability of a probiotic trial to reduce symptoms of maternal depression or anxiety in pregnancy. The secondary aim is to exploratorily compare the potential effect of probiotics, compared to placebo, on depressive and/or anxiety symptoms, maternal stress (i.e. reported/hair cortisol), maternal vaginal and intestinal microbiota, and by possibly affecting maternal mood and microbiota, maternal bonding to offspring, infant microbiota and infant crying.

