### Inclusion and exclusion criteria

The total sample of 40 healthy pregnant women will be recruited in the region of Wageningen and Nijmegen, The Netherlands. In order to be eligible to participate in this pilot trial, women must meet all of the following inclusion criteria:At least mild symptoms of depression or anxiety.Start daily probiotic/placebo product intake between 26 and 30 weeks gestational age and continue until delivery. The lower limit of ≥ 26 weeks and the upper limit of 30 weeks allow time to complete at least 8 weeks of probiotic intake prior to delivery. Gestational age is based on last menstrual period and the early ultrasound scan.

A potential participant who meets any of the following exclusion criteria will be excluded from participation in this pilot trial:Multiple pregnancy (increased obstetric risk).High suicidal risk according to suicidality subscale score on the MINI (see screening).Illegal drug use.History of psychoses and bipolar disorder.Inflammatory bowel disease (i.e. ulcerative colitis, Crohn’s disease).Other autoimmune disorders and/or treatment with immunosuppressive therapy.Known pre-existing diabetes mellitus, hyperemesis gravidarum, hypertensive disorders or liver or renal disease.Malignancy and/or treatment with radiation or chemotherapy.History of major gastro-intestinal surgery (e.g. colectomy).Hypersensitivity or allergy to any ingredients in the probiotic/placebo product.History of using oral multi-species probiotic Ecologic® Barrier.Presently using food containing probiotics (e.g. Actimel) and not willing to stop these at least 2 weeks prior to the start of the probiotic/placebo product intake.No mastery of the Dutch language.

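### Table 2 counts complications only up to delivery although it lists puerperal fever, and it merges common and rare events into one any-complication proportion with no onset rule

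*Protocol article*

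**What the plan says.** In the protocol article, Table 2 (under Secondary outcomes) has a row for pregnancy and delivery complications. Its measurement variable is a count, beginning "Number of pregnancy and delivery complications (i.e. hypertensive disorders of pregnancy" and ending with "small or large for gestational age (birth weight < p10 or > p90), puerperal fever, prolonged labor, premature rupture of membranes". Gestational diabetes, preterm birth, cesarean section and postpartum hemorrhage are also on the list. The participant-level metric is the final value. The aggregation per arm is "Proportion of participants diagnosed with pregnancy or delivery complications at delivery".

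The legend of Fig. 1 puts the last two measurements at 7 days (t3) and 1 month (t4) after birth.

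On entry, the abstract says "Forty healthy pregnant women with symptoms of depression or anxiety and uncomplicated pregnancies at randomization will be included", and Trial design also speaks of an uncomplicated pregnancy. The list under Inclusion and exclusion criteria has no criterion of that name. Its closest item is "Known pre-existing diabetes mellitus, hyperemesis gravidarum, hypertensive disorders or liver or renal disease". Intake starts between 26 and 30 weeks.

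Other rows of Table 2 bear on the same ground: "Gestational age at delivery", infections, and infant antibiotic use. Data monitoring and auditing and Serious adverse events describe separate adverse event channels.

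**The concern.** The row contradicts itself on timing. Puerperal fever by its nature arises after delivery, so a count closed at delivery leaves out an event that the row itself names. Postpartum hemorrhage fits the cut-off badly too.

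The aggregation also throws away what the variable collects. A number of complications becomes any or none, so a birth weight above p90 counts the same as eclampsia. A change in an uncommon, serious component is then blurred by the common ones.

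Last, the row does not say that a condition must be new since the start of intake. A condition diagnosed before the first sachet could be counted as an on-trial event.

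At stake is whether the pilot describes complications by arm correctly. Under Statistical analysis, the secondary outcomes are analysed to mimic the definitive trial, so a poor row is likely to be carried forward. Sample size calculation also names pregnancy complications among the reasons for enlarging the full trial to 150. Itemised counts would inform that allowance; one mixed proportion would not.

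**Working it through.** **Window.** The row closes at delivery but lists "puerperal fever, prolonged labor, premature rupture of membranes". Elsewhere Table 2 sets a later window where one is meant: breastfeeding is taken at t4 and infant antibiotics over the first month of life. The infections row is not a clear substitute for puerperal fever. It names fever, but its variable is limited to pregnancy while its aggregation runs over the whole study.

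**Onset.** The treatment and medication rows of Table 2 separate baseline status from new starts between t0 and t1. The complications row does not. With entry at 26–30 weeks, the delivery components can only occur after intake begins, and pre-existing hypertensive disorders are excluded. What remains is mainly gestational diabetes. The exclusion list does not name it, although the word uncomplicated may cover it.

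**Inputs for the dilution check.**
- 40 women, 20 per arm, and a full trial of 150, i.e. 75 per arm (Sample size calculation). The article's own ratio reproduces: 40/150 = 26.7%, stated as about 27%.
- Size component: "small or large for gestational age (birth weight < p10 or > p90". By construction 10% + 10% = 20% of a reference population, and 0.20 × 20 = 4 women per arm.
- All other rates are assumptions, because the article gives none. One component rises from 5% to 15% (1 versus 3 women expected in 20). The other components together affect 20%, 40% or 60% of women, independently of it.

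**Formula.** Composite rate = 1 − (1 − others) × (1 − component). With others at 20%: 1 − 0.80 × 0.95 = 24% versus 1 − 0.80 × 0.85 = 32%, and 0.32/0.24 = 1.33. Power is exact, for a two-sided Fisher test at 0.05 (the article does not state sidedness).

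| Other components | Composite rates | Difference | Risk ratio | Power, 20 per arm | Power, 75 per arm |
|---|---|---|---|---|---|
| none (component alone) | 5% v 15% | 10 points | 3.00 | 7.0% | 44% |
| 20% | 24% v 32% | 8 points | 1.33 | 4.7% | 15% |
| 40% | 43% v 49% | 6 points | 1.14 | 3.0% | 10% |
| 60% | 62% v 66% | 4 points | 1.06 | 3.0% | 6% |

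For 80% power at 20 per arm, a single component would have to go from 5% to about 45%.

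**Reading.** The composite shrinks a threefold rise to a ratio between 1.33 and 1.06. In the pilot, power is negligible whether or not the components are split. At the size of the full trial, the choice of aggregation makes a material difference.

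**The case against.** The strongest reply is that this is one descriptive row, not a safety endpoint. The six secondary objectives do not include obstetric safety, no progression criterion in Table 1 uses complications, and secondary results are to be read as preliminary. Adverse events are checked by an independent monitor, serious ones go to the ethics committee within set times, and the blind can be broken if needed. Gestational age, infections and infant antibiotics have their own rows. All of this stands. A reader might infer that obstetric safety rests on this single number, or that the later claim of negligible risk would. The documents do not say so: Potential harms states negligible risk as a prior judgement. The adverse event sections do, however, describe monitoring and reporting, not a summary by arm.

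Second, puerperal fever is named in the variable, its metric is the final value, and contacts exist at t3 and t4, so at delivery may be loose wording. The case report forms are in an additional file that is not shown. It would therefore be too much to say that the event will not be collected. The printed counting rule still excludes it.

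Third, tables by component could be left to an analysis plan. That would answer an omission. Here Table 2 states the aggregation and the time point.

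Fourth, randomization balances earlier conditions in expectation, and the entry rules remove most of them. That is right, and it keeps the onset point narrow.

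**Conclusion.** The point holds in a limited form. The window contradicts a listed component, the any/none proportion dilutes a change in any one component, and the row lacks the new-onset condition that neighbouring rows have. The first and third follow from the text alone. The size of the dilution (risk ratio 3 reduced to 1.33–1.06) rests on assumed rates and on independence; only the 20% for birth weight comes from the row's own definition.

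Two stronger readings are tempting and are not supported. One is that this row is why the pilot cannot show a harm. The first cause is 20 women per arm: 5% versus 15% has about 7% power even when analysed alone. The other is that prior conditions in general would be counted. The entry criteria reduce this mainly to gestational diabetes, on which the abstract and Trial design need to be read together with the exclusion list.

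The weight is modest: a correction to a stated rule in an exploratory pilot, worth making because it costs little and serves as the template for the full trial.

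**What to change.** In the complications row of Table 2:
- Run the window to t4, so that puerperal fever and postpartum hemorrhage fall inside it.
- Report the number and percentage of women with each listed complication by arm, beside the any-complication figure.
- Count conditions with onset after first intake, and list earlier ones as baseline characteristics.

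Reconcile the wording on uncomplicated pregnancies in the abstract and Trial design with the list under Inclusion and exclusion criteria, so that the status of gestational diabetes diagnosed before entry is explicit.

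The cost is table wording and, if the case report form does not already hold it, an onset date. The t3 and t4 contacts exist, so no visit or procedure is added. The downside is more table rows with small counts, which should be presented as description and not tested one by one.

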**Fig. 1 Fig1:**
[figure not shown]
Standard Protocol Items: Recommendations for Interventional Trials (SPIRIT) figure displaying the pilot trial design and the outcome measurements. After screening for eligibility (t-1), women sign the informed consent form and complete the baseline questionnaire (t0). Participants are then randomized in the probiotic or placebo arm and receive either the probiotic food supplement or placebo. After randomization, filling in the baseline questionnaire and collecting maternal vaginal and stool samples, women start using either the probiotic food supplement or placebo. Measurements take place at 26–30 weeks of pregnancy (baseline(t0); 34–38 weeks of pregnancy (t1); 7 days after birth (t3), and 1 month after birth (t4)).

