**Fig. 2 Fig2:**
[figure not shown]
Consolidated Standards of Reporting Trials (CONSORT) flow diagram indicating the participant’s flow through the study. After eligibility screening, women are randomized either to the probiotic or placebo arm. Follow-up measurements take place at 34–38 weeks of pregnancy (T1), 7 days after birth (T3), and 1 month after birth (T4). EPDS, Edinburgh Postnatal Depression Scale; LEIDS-R, Leiden Index of Depression Sensitivity-Revised; PRAQ-R, Pregnancy Related Anxiety Questionnaire-Revised

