#### Maternal stress

##### Pregnancy-related daily hassles

Pregnancy-specific daily hassles/stress are assessed with the Dutch translation of the Pregnancy Experience Scale (PES), a 43-item self-report inventory that measures maternal appraisal of daily, pregnancy-specific hassles and uplifts (Cronbach’s alpha between 0.91 and 0.95 when applied in its original language) [53]. The Dutch translation has been commonly used among pregnant Dutch women [54, 55]. Women rate the degree to which specific experiences constitute a hassle and uplift on a 5-point scale. The total score is the sum of intensities of hassles divided by the sum of intensities of uplifts; higher values indicate greater negative emotional bearing towards pregnancy hassles.

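### Table 2 carries the pregnancy-specific hassles scale (PES) to t4, one month after birth, where its change from baseline has no clear meaning (minor)

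*Protocol article*

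**What the plan says.** Table 2 (Secondary outcomes) lists the PES row as "Pregnancy-related daily hassles (PES) score Change from baseline to t1 and t4". The section on pregnancy-related daily hassles calls the instrument "a 43-item self-report inventory that measures maternal appraisal of daily, pregnancy-specific hassles and uplifts" and gives its scoring: "The total score is the sum of intensities of hassles divided by the sum of intensities of uplifts". Higher values are read as a more negative stance towards the hassles of pregnancy.

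The Fig. 1 legend dates the visits. The t1 visit is at "34–38 weeks of pregnancy (t1"), and the postnatal visits are at "7 days after birth (t3), and 1 month after birth (t4"). The Fig. 2 legend gives the same schedule.

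The neighbouring rows of Table 2 treat comparable scales differently. Pregnancy-related anxiety stops before delivery: "Pregnancy Related Anxiety Questionnaire-Revised (PRAQ-R) score Change from baseline to t1". The antenatal attachment scale (MAAS) also runs only from baseline to t1, and bonding after birth is measured by the postnatal scale (MPAS), from t3 to t4. The general hassles list (APL), which is not tied to pregnancy, runs to both t1 and t4.

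**The concern.** A change score assumes that the same thing is measured on both occasions. At baseline and t1 every woman is pregnant and can rate her current pregnancy-specific hassles and uplifts. At t4 nobody is. A woman given the scale then must either recall the pregnancy or rate experiences that have ended, and nothing in the article tells her which. Different women may choose differently.

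The secondary outcomes serve a purpose beyond this pilot. The Objectives section says they are collected so that effects and mechanisms can be properly assessed in a definitive trial. The statistical section says they are analysed as the definitive trial would be, and that effect sizes will inform its sample size. An outcome that does not apply at one of its time points could be carried forward unnoticed.

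**Working it through.** No arithmetic applies, because the point depends on no sample size, power or error rate. The check is a side-by-side reading of Table 2, the visit definitions and the instrument descriptions.

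| Scale | Tied to pregnancy, as described? | Change analysed in Table 2 | Woman pregnant at every visit used? |
|---|---|---|---|
| PRAQ-R | Yes | Baseline to t1 | Yes |
| MAAS | Yes (bond with the fetus) | Baseline to t1 | Yes |
| MPAS | No (postnatal) | t3 to t4 | Not applicable; both visits are after birth |
| APL | No (general hassles) | Baseline to t1 and to t4 | No, but the scale does not require it |
| PES | Yes | Baseline to t1 **and to t4** | Yes to t1; **no at t4** |

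1. **Table pattern.** Three instruments are pregnancy-bound as the article describes them: PRAQ-R, MAAS and PES. Two of the three stop at t1, and for bonding the table changes instrument after delivery. The PES alone continues past birth.
2. **Possible source.** The PES metric has the same wording as the APL row directly below it. That would fit a copying slip, but the article does not say so.
3. **Form of the scale.** The article mentions no postnatal adaptation of the PES, no recall instruction and no reference period for t4.
4. **Consequence.** The baseline-to-t1 difference compares two ratings of a current pregnancy. The baseline-to-t4 difference compares a rating of a current pregnancy with a rating of something the article leaves undefined. One of the two planned PES contrasts is therefore affected.
5. **Reach.** The other measures of maternal stress are the APL, at t1 and t4, and hair cortisol. Neither depends on the PES. None of the Table 1 progression criteria uses a PES score. The sample size section works from an effect on depressive symptoms (f = 0.187), not from the PES.

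**The case against.** Several objections limit the point.

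- **Low stakes.** No success criteria are set for any secondary outcome, and the statistical section calls all these analyses preliminary. This stands and is why the point is minor. Cautious interpretation does not, however, tell a reader what a t4 PES score represents.
- **Randomisation.** A reader might infer that the t4 change would show the end of pregnancy instead of a probiotic effect. The documents do not support that for the between-arm comparison. Both arms are one month postpartum at t4, so a shift common to both does not by itself create a difference between them. What remains is construct validity: the arms would be compared on a quantity without a clear meaning.
- **The whole stress outcome.** A reader might infer that the PES, or reported stress as a whole, is uninterpretable. It is not; the t1 contrast, the APL and hair cortisol are untouched.
- **Item content and the ratio.** It is tempting to say that all 43 items fail at t4, or that the ratio becomes unstable or undefined. The article gives neither the item wording nor the anchors of the 5-point scale. The ratio is undefined only if zero is an anchor and a woman rates every uplift zero, which cannot be established here.
- **The compliance criterion.** A reader might link blank PES items to the 90% questionnaire criterion, where 0.90 × 40 = 36 leaves room for at most 4 women with incomplete sets. That arithmetic holds for any cause of incompleteness and does not size this defect. The article does not say that an inapplicable item left blank makes a questionnaire unfilled.
- **Unseen material.** The Fig. 1 image and the data forms in Additional file 2 are not available. The PES may not be given at t4, or an adapted form may exist. This stands and makes part of the fix conditional. In either case the Table 2 entry would still need correction or explanation.

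**Conclusion.** The PES entry in Table 2 is inconsistent with the article's own description of the scale and with the way the same table handles the PRAQ-R, MAAS and MPAS. The baseline-to-t4 PES contrast would not be meaningful as specified, nor would an effect size computed from it. The conclusion assumes that the scale given at t4, if any, is the form described in the article, since no other is mentioned.

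Severity is minor: one time point of one exploratory secondary outcome, with no bearing on the progression decision as the criteria are written. The inconsistency in the table is certain. Whether the PES is actually administered at t4 is not.

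**What to change.** In Table 2, set the PES metric to change from baseline to t1 only, in line with the PRAQ-R and MAAS. If the PES is scheduled in the t4 questionnaire set, remove it there. Keep the APL as the reported-stress measure at t4. If a postnatal or recall form is in fact used, name it and report it as a separate outcome, as the table already does for postnatal bonding, not as a change from the antenatal score.

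The cost is one table cell and possibly a shorter t4 questionnaire; no interpretable contrast is lost. At submission 35 women had consented and 18 had completed the study, so some t4 PES data may already exist. The analysis restriction can be applied to all participants, while dropping the questionnaire would help only those still to reach t4.
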